#### Correlation analysis

Pearson correlation analysis will be performed between electrophysiological parameters, MRI parameters, and clinical function scores in cM1 LF group and cPMd HF group. The statistical threshold will be set to *p* < 0.05.

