#### Rs-fMRI

A total of 90 network nodes will be defined according to Anatomical Automatic Labeling (AAL) atlas. Pearson correlation analyses will then be performed on the preprocessed RS fMRI data, which will result in one 90 × 90 correlation matrix representing the functional connection between each two network nodes. A threshold will be used to binarize the matrix, and all correlation coefficients greater than the threshold will be assigned 1, otherwise 0. Topology attributes, including global network efficiency (Eg), local network efficiency (El), network betweenness, and clustering coefficient will be calculated for each patient based on the correlation matrix.

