#### Group-level analysis

All statistical analyses will be performed using SPSS software (SPSS 25.0, SPSS Inc., Chicago, Illinois). The intention-to-treat principle will be used for the analysis of functional and electrophysiological data. One-way analysis of variance (ANOVA) will be used to compare the demographic characteristics and baseline assessment (T0) of all outcomes among groups. To compare the treatment effects of different rTMS protocol, a two-way mixed design ANOVA with between-subject factor “Group” and within-subject factor “Time” will be performed for the clinical and electrophysiological changes. Moreover, Bonferroni correction will be employed for post hoc multiple comparisons. *P* < 0.05 will be considered statistically significant for all analyses.

For rs-fMRI and DTI data, a two-way mixed design ANOVA will be performed, with between-subject factor “Group” and within-subject factor “Time” on the data generated in the data processing step, including Eg, El, network betweenness, clustering coefficient, and FA AI. For tb-fMRI data, a whole brain paired T-test will be performed between the task state blocks and baseline blocks in the FC group, and the voxels whose t value is higher than the threshold will be regarded as the activated brain region. For cM1-LF, cPMd-HF, and CON groups, a two-way mixed design ANOVA, with between-subject factor “Group” and within-subject factor “Time” will be performed within the former activated brain region. The most significant point of “Group” × “Time” effect in the activated brain region will be used as the center to construct spherical balls with a radius of 6 mm, and the spherical balls will be regarded as the ROIs. Finally, to obtain the effective connectivity of each patient at different time points, the average time series of all voxels in each ROI will be subjected to dynamic causal model (DCM) analysis.

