In addition to potential clinical influence, the study will elucidate the underlying mechanism of brain plasticity though longitudinal analysis of multimodal fMRI data scanned before and after the intervention, and during the follow up. It is worth noting that rest-state fMRI will provide information about the changes of brain networks, task-based fMRI will display the brain activation model of specific task instantly, and DTI will provide insights into the remodeling of motor pathway. Collectively, the results will help us to further understand the neural effects of different protocols of rTMS therapy in stroke rehabilitation. Furthermore, the joint analysis of neuroimaging data and functional changes will indicate the cut-off that separates mildly from severely affected patients, ultimately guiding application of tailored stimulation parameters for rTMS (i.e. low-frequency rTMS on cM1 or high-frequency rTMS on cPMd). In conclusion, this study will provide a theoretical basis for clarifying the bimodal balance-recovery model of stroke, provide biological markers for predicting the functional prognosis in chronic stroke patients after rTMS therapy, and provide a strategy for individualized rTMS treatment for stroke in future studies and clinical practice.

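### Correlations across three measurement domains in two arms are judged at an uncorrected p < 0.05, so several chance associations could be reported as prognostic markers

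*Protocol article*

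**What the plan says.** Under Correlation analysis the protocol article states: "Pearson correlation analysis will be performed between electrophysiological parameters, MRI parameters, and clinical function scores in cM1 LF group and cPMd HF group". The next sentence fixes the criterion: "The statistical threshold will be set to *p* < 0.05". No pair of measures is singled out, and the section does not say which visits or change scores are used.

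Under Group-level analysis, p < 0.05 "will be considered statistically significant for all analyses". The one multiplicity provision follows the ANOVA of clinical and electrophysiological data: "Bonferroni correction will be employed for post hoc multiple comparisons".

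Under Rs-fMRI, "A total of 90 network nodes will be defined according to Anatomical Automatic Labeling (AAL) atlas". The measures sent to the imaging ANOVA are listed as "including Eg, El, network betweenness, clustering coefficient, and FA AI".

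The Discussion says that the study will "provide biological markers for predicting the functional prognosis in chronic stroke patients after rTMS therapy". It also says that jointly analysing imaging and functional change will give a cut-off for choosing the stimulation strategy. The Aims and hypotheses section names that cut-off as well.

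**The concern.** The correlation section is the only analysis described in the article that links imaging or electrophysiology to clinical function, so the marker claim has to rest largely on it. It covers three whole domains in two arms and applies the single-test threshold to each correlation. The Bonferroni step concerns post hoc comparisons and does not reach this family.

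This is a stated rule and not merely a detail left to a statistical analysis plan: a plan that corrected for multiplicity would have to replace the threshold printed here.

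At stake is the credibility of any reported marker. With 20 patients per arm, a correlation must be fairly large to reach p < 0.05 at all, so a chance finding will look strong on the page and may be read as a usable predictor.

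**Working it through.** The article gives no number of tests, so there is no figure of its own to reproduce. The counts below are built from its named measures.

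**Inputs**
- Clinical measures, C. The clinical assessment section names 8: Brunnstrom stage, MMT, MAS, NIHSS, FM-UL, ARAT, WMFT and MBI. A narrow reading keeps only the three arm-function scales (FM-UL, ARAT, WMFT), so C = 3.
- Electrophysiological measures, E. The same section names 3 kinds: RMT, MEP amplitude and MEP latency. Taking each on both sides gives E = 6. This is an upper assumption, because patients without an MEP on the affected side have no amplitude or latency there.
- MRI measures, M = 5: global efficiency, local efficiency, betweenness, clustering coefficient and FA AI, each taken as one value per patient. Task activation and effective-connectivity measures are not counted.
- Arms: 2. Threshold: 0.05.

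**Formulas**
- Tests at one time point = 2 × (C×E + C×M + E×M), assuming that all cross-domain pairs are examined.
- Expected false positives if no association is real = tests × 0.05. This expectation does not require the tests to be independent.

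**Results, one time point**

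| Reading | C, E, M | Pairs per arm | Tests in two arms | Expected false positives |
|---|---|---|---|---|
| Three arm scales only | 3, 3, 5 | 9 + 15 + 15 = 39 | 78 | 3.9 |
| All clinical scales, E = 3 | 8, 3, 5 | 24 + 40 + 15 = 79 | 158 | 7.9 |
| All clinical scales, both sides | 8, 6, 5 | 48 + 40 + 30 = 118 | 236 | 11.8 |

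More visits or change windows multiply these counts. Two windows on the middle reading give 2 × 158 = 316 tests and 15.8 expected. Three time points on the widest give 3 × 236 = 708 tests and 35.4 expected.

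**Size of correlation needed.** The smallest significant |r| is t/√(n − 2 + t²), with t the two-sided 5% point on n − 2 degrees of freedom (the article does not state sidedness; two-sided is assumed).
- n = 20: t = 2.101, so |r| = 2.101/√(18 + 4.41) = 0.44.
- n = 14 (20 × 0.70, after the assumed 30% dropout): t = 2.179, so |r| = 2.179/√(12 + 4.75) = 0.53.

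**Conditional part.** If betweenness is tested separately at each of the 90 nodes, 90 × 0.05 = 4.5 false-positive nodes are expected for each ANOVA effect. The chance of at least one is 1 − 0.95^90 = 0.99 if the tests are independent, which network measures are unlikely to be.

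**The case against.** The strongest reply is that these are secondary, mechanistic analyses in a condensed article. The abstract gives the main purpose as comparing the two stimulation regimens, and the marker statement is one clause of the Discussion. The list of pairs could properly sit in an analysis plan that is not shown, and the article never says that every pairing will be tested. This is right as far as it goes: the missing list is not the point, and the counts are a range that rests on an assumption. What remains is the printed threshold. Even if the electrophysiology-to-MRI pairs are dropped from the narrowest reading, 2 × (9 + 15) = 48 tests and 2.4 expected false positives are left.

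A reader might also infer that 90 nodal tests are planned. Adding 90 betweenness values to the four other MRI measures, with C = 8 and E = 6, would give 2 × (48 + 752 + 564) = 2,728 correlations and about 136 false positives. The documents do not support stating this as fact. The Rs-fMRI section uses the 90 nodes to build the connectivity matrix and then lists betweenness beside network-level summaries. That wording fits one value per patient, or the cPMd alone, which is the only region whose betweenness the article discusses. The nodal figures therefore stay conditional.

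The use of Pearson coefficients is a minor matter. The section does not say that Brunnstrom, MMT or MAS grades will be correlated, and for the summed scales Pearson is common practice.

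**Conclusion.** The point holds in limited form. An uncorrected 0.05 threshold is laid down for a family of cross-domain correlations, and prognostic markers are expected from the study. On the article's own list of measures, about 4 to 12 chance findings per time point are expected. This assumes that all cross-domain pairs are examined and that no true associations exist; real associations would lower the number of false findings but would not separate them from the true ones.

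Two stronger conclusions do not follow. That hundreds of tests are planned is not stated, and at one time point the count falls to 158 or 78 on narrower readings. Nor is the trial's clinical conclusion undermined: the Group x Time comparison of function does not depend on the correlations. The harm is confined to the marker, mechanism and cut-off claims. It deserves correction because the remedy is cheap.

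**What to change.** In the Correlation analysis section, replace the blanket p < 0.05 by three statements.

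1. A short pre-specified list, for example T0 to T1 change in FM-UL against T0 to T1 change in betweenness of the region taken to represent cPMd, and against FA AI. The article does not show that the 90-region atlas has a separate cPMd node, so the representing region must be named. Two pairs in two arms make 4 tests, with 4 × 0.05 = 0.2 false positives expected.
2. False discovery rate control at 5% over all other correlations, and over any node-wise tests if betweenness is analysed by node. The text should say whether it is.
3. A label of hypothesis-generating for everything outside the short list, with the Discussion's marker claim worded to match.

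As a minor addition, use Spearman coefficients for short ordinal grades if these are correlated.

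The cost is wording and fewer nominally significant correlations; no data, patients or procedures are added. A Bonferroni correction of the whole family would be harsher: for 158 tests the threshold is 0.05/158 = 0.00032, and the required |r| rises from 0.44 to 0.72 at n = 20 and from 0.53 to 0.82 at n = 14. That is why a short list with false discovery rate control over the rest is preferable.

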### Quality control

Huashan Hospital will monitor the following aspects of the trial regularly and strictly: the work division and training for the research staff, file management, informed consent, protocol compliance, subject recruitment, filling in the CRF, intervention, quality assured system, statistical analysis, and data management.

## Discussion

Several studies conducted in recent years have confirmed that rTMS can effectively improve the motor function of stroke patients with hemiplegia [7–10]. However, negative results have also been reported, with some studies even observing functional regression in some patients [11–16]. These evidences suggest that the standardized rTMS protocol based on the IHI imbalance theory between bilateral M1 has its limitation in clinical practice [19, 20]. In chronic stroke patients with severe motor impairments, extensive damage to affected pathway of motor output hinders the effects of affected M1 in motor recovery, thereby rendering classic rTMS protocol ineffective [18]. Thus, this study will focus on cPMd based on a more recent “bimodal balance-recovery model” [23]. Evidence suggests that inhibition of cPMd directly impairs movement of the paretic extremity in severe patients [33], and the betweenness centrality of cPMd is significantly positively correlated with the motor score [35]. Therefore, we hypothesized that cPMd is more likely to be the key factor for functional recovery of severely affected patients. This hypothesis will be verified by conducting a randomized controlled trial, which will directly compare the effects of low-frequency rTMS on cM1, high-frequency rTMS on cPMd, and sham-stimulation. It is expected that the findings of the study will facilitate development of a new protocol of rTMS therapy for treating severely affected stroke patients.

In addition to potential clinical influence, the study will elucidate the underlying mechanism of brain plasticity though longitudinal analysis of multimodal fMRI data scanned before and after the intervention, and during the follow up. It is worth noting that rest-state fMRI will provide information about the changes of brain networks, task-based fMRI will display the brain activation model of specific task instantly, and DTI will provide insights into the remodeling of motor pathway. Collectively, the results will help us to further understand the neural effects of different protocols of rTMS therapy in stroke rehabilitation. Furthermore, the joint analysis of neuroimaging data and functional changes will indicate the cut-off that separates mildly from severely affected patients, ultimately guiding application of tailored stimulation parameters for rTMS (i.e. low-frequency rTMS on cM1 or high-frequency rTMS on cPMd). In conclusion, this study will provide a theoretical basis for clarifying the bimodal balance-recovery model of stroke, provide biological markers for predicting the functional prognosis in chronic stroke patients after rTMS therapy, and provide a strategy for individualized rTMS treatment for stroke in future studies and clinical practice.

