## Abstract

**Background:**

Previous studies have revealed that low frequency repeated transcranial magnetic stimulation (rTMS) on the contralesional primary motor cortex (cM1) is less effective in severe stroke patients with poor neural structural reserve than in patients with highly reserved descending motor pathway. This may be attributed to the fact that secondary motor cortex, especially contralesional dorsal premotor cortex (cPMd), might play an important compensatory role in the motor function recovery of severely affected upper extremity. The main purpose of this study is to compare the effectiveness of low frequency rTMS on cM1 and high frequency rTMS on cPMd in subcortical chronic stroke patients with severe hemiplegia. By longitudinal analysis of multimodal neuroimaging data, we hope to elucidate the possible mechanism of brain reorganization following different treatment regimens of rTMS therapy, and to determine the cut-off of stimulation strategy selection based on the degree of neural structural reserve.

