**Methods/design:**

The study will be a single-blinded randomized controlled trial involving a total of 60 subcortical chronic stroke patients with severe upper limb motor impairments. All patients will receive 3 weeks of conventional rehabilitation treatment, while they will be divided into three groups and receive different rTMS treatments: cM1 low frequency rTMS (*n* = 20), cPMd high frequency rTMS (*n* = 20), and sham stimulation group (*n* = 20). Clinical functional assessment, multimodal functional MRI (fMRI) scanning, and electrophysiological measurement will be performed before intervention, 3 weeks after intervention, and 4 weeks after the treatment, respectively.

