The interhemispheric inhibition (IHI) model, which is commonly used as the fundamental theory for standardized rTMS treatment, was first proposed by Murase in 2004 [22], which suggests that the bilateral primary motor cortexes (M1) are connected through the corpus callosum in a balance of competing inhibition in healthy individuals. However, the IHI balance is disturbed after the onset of stroke, thereby leading to over activation of the contralesional hemisphere. Specifically, damage to the affect hemisphere weakens its inhibitory effect on the contralesional hemisphere, ultimately resulting in abnormally increased excitability of cM1. Notably, the over activation of cM1 will in turn inhibit the affect M1, causing a vicious circle. The disrupted balance between bilateral M1 will eventually hinder the motor output and impede the recovery of upper limb motor function in stroke survivors. Ideally, according to the standardized treatment protocol [19, 20], high-frequency rTMS is able to increase the excitability of affected M1, whereas low-frequency rTMS is capable of reducing the excitability of cM1, thereby enabling the disrupted IHI to reach a new equilibrium. However, some studies have found that the standardized rTMS protocol is not suitable for all stroke patients [11, 12]. It is worth noting that patients with severe hemiplegia seem to be less suitable for this standardized rTMS protocol [19]. This has led to some researchers questioning the value of classic IHI imbalance theory in clinical practice. Pino et al. [23] proposed the bimodal balance-recovery model in stroke recovery, which suggests that determining the mode of recovery to be adopted depends on the degree of damage to the affected hemisphere, namely structural reserve. For example, in patients with less damage (higher structural reserve), the classic IHI imbalance mode will dominate the recovery process, and the increased activation of contralesional hemisphere will not be conducive to motor recovery. In such cases, standardized low frequency rTMS of cM1 can exert therapeutic effects by inhibiting this abnormal excitability. In contrast, for patients with low structure reverse, the recovery process will be dominated by the compensatory mode because the increased motor cortex excitability on the unaffected side will be conducive to rehabilitation. In this case, the standardized low-frequency rTMS protocol might not be effective, and thus applying high-frequency rTMS on cM1 is a better option. Taking these two recovery models together, we believe that if we can identify the cut-off of structural reserve, we might be able to evaluate the real effects (inhibitory or compensatory) of the contralesional hemisphere on motor output. This will aid in selecting the optimum rTMS stimulation strategy on contralesional hemisphere (low frequency or high frequency).

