### Aims and hypotheses

This study will conduct a longitudinal, single-blinded, randomized controlled trial to verify the clinical effects of different protocols of rTMS therapy on functional recovery of chronic subcortical stroke patients with severe hemiplegic upper limb. To the best of our knowledge, this is the first study to compare the effects of low-frequency rTMS on cM1 and high-frequency rTMS on cPMd. We expect that the findings will provide vital information about the optimal rTMS strategy. Multimodal fMRI scanning and electrophysiological measurements will be performed longitudinally to elucidate the underlying neural mechanism of brain reorganization after different parameters of rTMS therapy. We hypothesize that high-frequency rTMS on cPMd might be the optimal protocol for motor functional recovery in chronic subcortical stroke patients with severe hemiplegia. This clinical effect may be attributed to the specific remodeling patterns of structural, functional, or effective connectivity of homologous or allogeneic cortexes within or between hemispheres through multimodal neural imaging analysis. Furthermore, joint analysis of the clinical and neuroimaging results might identify the cut-off of structural reserve that determines the application of high/low frequency rTMS on contralesional hemisphere to achieve maximum functional recovery of the paretic upper limb.

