### Inclusion and exclusion criteria

A total of 60 eligible patients will be recruited from Huashan Hospital, Fudan University. The inclusion and exclusion criteria are listed in Table 1.

**Table 1 Tab1:** Inclusion and exclusion criteria

Criteria	Description
Inclusion criteria	➤ First-ever stroke ➤ Subcortical stroke diagnosed by head CT or MRI ➤ Clear consciousness and stable vital signs ➤ 18–80 years old ➤ 3–12 months since stroke onset ➤ Unilateral hemiplegia, Brunnstrom stage of affected hand ≤ IV ➤ Right-handed
Exclusion criteria	➤ Severe speech, attention, hearing, vision, sensation, intelligence, mental, or cognitive impairments (MMSE score < 27) ➤ Severe spasticity (Modified Ashworth Spasticity Scale > 2) or pain (Ten-point Visual Analog Scale > 4) of the affected side ➤ Bone, joint, and muscle diseases, other serious nervous system diseases, malignant tumors, and serious heart, lung, liver, and kidney damage ➤ Still enrolled in any rehabilitation or drug studies ➤ Metal implant, magnetic sheet, or cardiac pacemaker ➤ Alcohol or drug addiction ➤ Epilepsy

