#### DTI

The bilateral posterior limb of internal capsule (PLIC), bilateral cerebral peduncle, and corpus callosum of each patient will be delineated manually by two radiologists. For each patient, the common part of the results recorded by the two radiologists will be adopted as the regions of interest (ROIs). The mean fractional anisotropy (FA) will be calculated with all the ROIs for each hemisphere. Notably, FA asymmetery index (FA AI) is defined by the following formula:

$$FA\ AI=\frac{\left({FA}_c-{FA}_a\right)}{\left({FA}_c+{FA}_a\right)}$$where FAc is the FA of the contralesional hemisphere and FAa is the FA of the affected hemisphere. FA AI can be used to quantitatively evaluate the structural integrity of CST and corpus callosum.

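### A mild-versus-severe cut-off cannot be estimated from severe patients only, and the stated correlations cannot supply a structural-reserve cut-off for choosing the rTMS strategy

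*Protocol article*

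**What the plan says.** The cut-off appears in three places in the protocol article.

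- **Abstract, Background:** the authors hope "to determine the cut-off of stimulation strategy selection based on the degree of neural structural reserve".
- **Aims and hypotheses:** a joint analysis of clinical and imaging results might "identify the cut-off of structural reserve that determines the application of high/low frequency rTMS on contralesional hemisphere".
- **Discussion:** the hedge is gone and the cut-off is one of clinical severity: "the joint analysis of neuroimaging data and functional changes will indicate the cut-off that separates mildly from severely affected patients". The same sentence says this will guide tailored stimulation.

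The Abstract (Methods/design) describes "a total of 60 subcortical chronic stroke patients with severe upper limb motor impairments". The operational limit in Table 1 is "Unilateral hemiplegia, Brunnstrom stage of affected hand ≤ IV". Healthy controls are scanned once, at T0, and receive no rTMS.

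The DTI section provides the measure of reserve: "FA AI can be used to quantitatively evaluate the structural integrity of CST and corpus callosum". Under Group-level analysis, FA AI is an outcome in a Group by Time ANOVA. The one stated analysis joining imaging with function is under Correlation analysis: "Pearson correlation analysis will be performed between electrophysiological parameters, MRI parameters, and clinical function scores in cM1 LF group and cPMd HF group", at p < 0.05.

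**The concern.** A cut-off for choosing between two treatments is the value of a baseline marker at which the better treatment changes. Estimating it requires the treatment difference as a function of that marker, that is, a treatment-by-marker interaction, in patients who cover the region where the change may occur.

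The Discussion promises a boundary between two clinical groups, only one of which is treated. The stated correlations describe how marker and function go together among patients given a particular active treatment. Patients with more reserve may simply recover more whatever they receive, and such a marker would correlate with function in both arms without favouring either treatment.

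The risk is that prognostic associations in small arms are later read as a rule for selecting stimulation, which the Discussion offers for future studies and practice.

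**Working it through.** **1. Mild-versus-severe boundary.** The Abstract, Aims and hypotheses, and Study design all describe the patients as severe, and Table 1 caps the Brunnstrom hand stage. No mild stratum is treated, so the data contain no treatment effect on the mild side of the boundary. This needs no arithmetic.

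**2. What a correlation can and cannot give.** Let x be T0 FA AI. By the article's formula, a larger value means lower FA on the affected side. Write mean improvement as

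- cM1-LF: a1 + b1·x
- cPMd-HF: a2 + b2·x

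The lines cross at x* = (a1 − a2)/(b2 − b1). Pearson r in an arm does not depend on a1 or a2. Adding a constant c to every cPMd-HF improvement moves x* by −c/(b2 − b1) and leaves both correlations unchanged, so the two r values cannot determine x*. If b1 = b2, both arms can show the same strong correlation and there is no crossing: the marker is purely prognostic. Pooling the two arms gives one association and does not identify x* either.

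**3. The plan's own sample size.** The article gives no figure for the cut-off aim; its only sizing figure is 20 per arm (Sample size calculation: FM-UL 30 to 43, SD 17, power 80%, alpha 0.05, dropout 30%; two-sided assumed).

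- Single-group pre-post, normal formula: ((1.96 + 0.842) × 17/13)² = 13.4, so 14; 14/0.70 = 20. This reproduces the stated figure.
- Two-arm comparison of means with the same inputs: 2 × 13.4 = 26.8, so 27; 27/0.70 = 38.6, so 39. This does not.

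The stated size therefore agrees with a within-group change. It was not derived for an interaction.

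**4. Precision at that size.** Use n = 20, and n = 14 after dropout (20 × 0.70).

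| Quantity | Formula | n = 20 | n = 14 |
|---|---|---|---|
| Critical r in one arm (two-sided 0.05) | t-based | 0.444 | 0.532 |
| r detectable in one arm, 80% power | tanh(2.80/√(n−3)) | 0.59 | 0.69 |
| SE of Fisher-z difference | √(2/(n−3)) | 0.343 | 0.426 |
| z gap for 80% power | 2.80 × SE | 0.96 | 1.19 |
| Same gap as opposite correlations | ± tanh(gap/2) | ±0.45 | ±0.54 |
| Same gap as r against 0 | tanh(gap) | 0.74 | 0.83 |

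Significance in one arm only is not evidence of a difference. At n = 20, r = 0.50 is significant and r = 0.30 is not. Their z difference is 0.549 − 0.310 = 0.239, and 0.239/0.343 = 0.70, well short of 1.96.

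**5. The interaction itself (assumed inputs, illustration only).** The target is a difference in slopes; the Fisher-z figures are a guide to it. A simulation took reserve as uniform on a 0–1 scale and residual SD 1. The treatment difference ran from one SD in favour of one arm at the bottom of the scale to one SD in favour of the other at the top, crossing at 0.5.

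| Reserve range enrolled | Interaction power, n = 20 (14) | Central 95% of crossing estimates, n = 20 (14) |
|---|---|---|
| Full, 0–1 | 40% (29%) | −0.29 to 1.24 (−0.70 to 1.87) |
| Lower half, 0–0.5 | 14% (11%) | −2.30 to 2.70 (−2.16 to 2.64) |

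Even with the full range enrolled, the crossing estimates spread beyond the whole scale. The article gives no FA AI range, so which row is closer to this trial is unknown.

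**The case against.** The strongest reply is that the aim in the Abstract and in Aims and hypotheses concerns structural reserve, not clinical severity. Entry is clinical: no criterion restricts FA, FA AI or MEP status, both MEP-positive and MEP-negative patients are provided for, and the FM-UL figures used for sizing have an SD of 17. Reserve may well vary among those enrolled. This stands. A reader might infer that any reserve cut-off lies outside the data and that the aim cannot be met; the documents do not support that. The Background does tie the low-frequency strategy to the high-reserve end ("in patients with less damage (higher structural reserve), the classic IHI imbalance mode will dominate the recovery process"), which makes coverage of the crossing region uncertain but does not show that it is missing.

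A second reply is that the Correlation analysis section never mentions the cut-off. The article assigns it to a joint analysis whose method may sit in an analysis plan not shown here. This also stands in part: a reader might infer that the trial will derive its threshold from these correlations, and no section says so. What remains is that the one analysis actually stated for linking imaging to function does not serve the aim, and no analysis plan could supply mild patients.

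Third, leaving sham out of the correlations is not fatal. The contrast between the two active arms is identified from those arms; sham helps to show prognosis without active stimulation but is not required.

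Finally, the aim is secondary and mostly hedged. The Abstract gives the comparison of effectiveness as the main purpose, and only the Discussion says the cut-off will be indicated. That lowers the weight of the point.

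**Conclusion.** The point holds in two parts. The Discussion's cut-off between mildly and severely affected patients cannot be estimated, because only patients described as severe are treated. The structural-reserve cut-off remains possible in principle, but Pearson correlation in the two active arms cannot provide it, since it contains no treatment-by-reserve contrast and no location for a crossing.

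Any such analysis will be imprecise: a between-arm Fisher-z gap of about 0.96 at 20 per arm, or 1.19 at 14, is needed for 80% power. These figures assume a two-sided 5% test, equal arms and the article's 30% dropout. The simulated figures rest on assumed inputs and only illustrate the order of size.

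Severity is moderate. The randomized comparison and its Group by Time ANOVA do not depend on this aim.

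**What to change.** 1. For the cut-off aim, add one model: follow-up FM-UL (for example at T1) on baseline FM-UL, arm, T0 FA AI and arm × FA AI. Report the cPMd-HF versus cM1-LF interaction with its 95% CI. Including the sham arm is useful for showing prognosis.
2. Report any crossing value of FA AI as exploratory, with its CI, and only if it lies inside the observed FA AI range. State that precision is low at 14–20 per arm.
3. Keep the correlations as descriptive, and say that they do not inform the choice of treatment.
4. Reword the Discussion sentence to effect modification within severely affected patients, and drop the mild-versus-severe cut-off.

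The cost is analysis wording and a narrower claim. DTI at T0 and FM-UL at T0, T1 and T2 are already scheduled, so no new patients or measurements are needed. Trial status says recruitment was not complete at submission.
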